#### Demographic data

3.9.2

Continuous variables will be expressed as the means ± standard deviation (SD), and categorical variables will be expressed as n (%). The chi-square test and independent *t* test will be used to examine differences in basic demographic variables, including sex, age, occupation, and medical history.

#### Outcome analysis

3.9.3

##### Primary outcomes

3.9.3.1

The difference between the K-WOMAC score measured during screening and that measured after the last treatment session (V10) will be determined for each participant. The statistical significance of the difference in the K-WOMAC for each group will be determined using a paired *t* test or Wilcoxon signed rank test with a 5% statistical significance level. The independent *t* test or Wilcoxon rank sum test will be used to determine the statistical significance of the efficacy of acupuncture in each group. The results will be adjusted for covariant factors, which are factors that can affect the results of an analysis.

##### Secondary outcomes

3.9.3.2

The paired *t* test will be used to analyze the changes in the NRS, risk of falling, and range of motion (ROM) from the baseline to V10 in each group. Student's *t* test will be used to analyze these changes between different groups. A repeated-measured ANOVA will be used to analyze the differences in the changes in all variables, including the K-WOMAC score that occur within a group before the treatment.

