#### Secondary outcome

3.8.2

The secondary outcome assessment measures the change from the baseline in the numerical rating scale (NRS). The time frame is as follows: screening, baseline, and days 5, 11, 21, 28, and 84. The NRS range is 0 to 10, with 0 being no pain and 10 being the worst pain possible. In addition, the following outcome assessments are surveyed as a secondary outcome measurement: Change from the baseline in a physical condition related to mobility, which is a 5-m walking test at a comfortable speed of −5 mWT (meters/second) at every visit (time frame: screening, days 11 and 84); change from the baseline in a physical condition related to endurance, which is a sit-to-stand test (seconds) at every visit (time frame: screening, days 11, 84); change from the baseline in the timed up and go test, which is a functional test for evaluating the time to rise from a chair, walk 3 m, turn around, walk back to a chair and sit down (abnormal cutoff value >12 s) at every visit (time frame: screening, day 11, day 84); change from the baseline in the alternative step test, which is a functional test measuring the clinical balance performance, and it has been shown to predict fall risk among elderly subjects (seconds) at every visit (time frame: screening, day 11, day 84); and change from the baseline in the range of motion test, which compares the flexion and extension angle using a long-arm goniometer between the experimental and comparator groups (time frame: screening, baseline, days 5, 11, 28, and 84).

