#### General principle for statistical analysis

3.9.1

An intention-to-treat (ITT) analysis will be performed as the primary analysis for patients who receive acupuncture at least once. A per-protocol analysis will also be performed for participants who have completed the study after excluding dropouts.

For intergroup comparisons, an independent *t* test will be performed for continuous variables if normality is satisfied. If normality is not satisfied, the Wilcoxon rank-sum test, a nonparametric statistical technique, will be performed. For comparisons between different time points within each group, a paired *t* test or Wilcoxon signed rank test will be used. An analysis of covariance (ANCOVA) adjusted for covariant factors that show significant differences with respect to the baseline in each treatment group and the initial baseline outcomes will be additionally determined. For categorical variables, the chi-square test or Fisher's exact test will be used.

All statistical analyses will be two-tailed with a 5% significance level. The last observation carried forward (LOCF) method will be used to handle missing values. Multiple imputation or a regression analysis will be additionally used to examine differences in the results.

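### Outcomes are defined into follow-up (K-WOMAC to FU2, secondary outcomes to day 84), but the outcome-specific between-group tests stop at V10 and the only longitudinal method is described as within a group

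*Protocol article*

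**What the plan says.** All references are to the protocol article.

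- **Endpoint definitions (3.8.1, 3.8.2).** For NRS, "The time frame is as follows: screening, baseline, and days 5, 11, 21, 28, and 84". For ROM, "time frame: screening, baseline, days 5, 11, 28, and 84". For the 5-m walk, "time frame: screening, days 11 and 84"; the sit-to-stand, timed up and go and step tests have the same schedule. K-WOMAC is defined at screening, V10 and FU2.
- **Secondary analysis (3.9.3.2).** The paired *t* test covers the change "from the baseline to V10 in each group". The between-group sentence follows directly: "Student's *t* test will be used to analyze these changes between different groups". Its subject is the changes just named, so it also ends at V10.
- **Longitudinal method (last sentence of 3.9.3.2).** A repeated-measures ANOVA is planned for differences in the changes in "all variables, including the K-WOMAC score that occur within a group before the treatment".
- **Primary analysis (3.9.3.1).** The K-WOMAC change is taken from screening to V10, and the between-group test applies to that change.
- **General rule (3.9.1).** "For intergroup comparisons, an independent *t* test will be performed for continuous variables if normality is satisfied"; otherwise the Wilcoxon rank-sum test is used, with ANCOVA in addition. No visit is named.

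**The concern.** The aim in section 2 is a comparison of acupuncture plus usual care with usual care alone. Assessments after V10 serve to show whether any difference persists once treatment has ended. For that question the plan's outcome-specific sections offer only a method described as within a group. Both arms are recovering from knee replacement, so change over time within an arm mixes surgical recovery with any treatment effect. Finding significant change in one arm and not in the other would not be a comparison of the arms either.

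At stake is how follow-up results are produced and read. In an open-label trial of 50 patients, leaving open which follow-up contrasts count, and how they rank against V10, makes selective emphasis easier. Within-group improvement could also be presented as evidence of a lasting effect.

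**Working it through.** **Step 1. Count the secondary post-baseline points in 3.8.2.**

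| Outcome | Day 5 (during treatment) | Day 11 (V10) | Follow-up | Total |
|---|---|---|---|---|
| NRS | 1 | 1 | 3 (days 21, 28, 84) | 5 |
| ROM | 1 | 1 | 2 (days 28, 84) | 4 |
| Four physical tests | 0 | 4 | 4 (day 84) | 8 |
| All | 2 | 6 | 9 | 17 |

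Check: 2 + 6 + 9 = 17.

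**Step 2. Match each column to the between-group test in 3.9.3.2.** That test covers the change to V10, which is the 6 points at day 11. It covers 0 of the 9 follow-up points. The 2 points at day 5 also have no assigned test, but they fall during treatment and say nothing about persistence, so they are not counted here.

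**Step 3. Do the same for K-WOMAC.** There are two post-treatment assessments, V10 and FU2. Section 3.9.3.1 tests the first. FU2 has no outcome-specific between-group test: 0 of 1. (FU2 is labelled day 21 in 3.8.1 but 28 days in Table 1; these need reconciling, and the visit label is used here.)

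**Step 4. Ask whether the ANOVA sentence fills the gap.** There are two ways to read it.

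- *Literal:* it concerns changes before treatment, so it uses no follow-up data.
- *Charitable:* the phrase is a slip for a comparison with the pre-treatment value. Follow-up visits then enter, but the changes are still described as within a group, and no group or group-by-time term is stated.

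On neither reading is a between-group follow-up contrast specified.

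**Step 5. Ask whether 3.9.1 fills the gap.** It says which test to use when groups are compared on a continuous variable. It does not say at which visits they are compared. It therefore permits tests at days 21, 28 and 84 without specifying them.

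**Step 6. Check what is unaffected.** The sample size in 3.3 was set for one K-WOMAC comparison and reproduces:

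- pooled SD = √((4.05² + 4.16²)/2) = 4.105
- standardised difference = 3.60/4.105 = 0.877
- two-sided α = 0.05 and 80% power, noncentral *t*: 22 per group (power 0.811)
- 10% dropout: 22/0.9 = 24.4, rounded up to 25 per group

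Nothing in this point changes those figures.

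**The case against.** The strongest reply is that 3.9.1 already supplies a valid test. A per-visit *t* test or Wilcoxon test on change scores, with baseline-adjusted ANCOVA in addition, is legitimate at any visit and needs no repeated-measures model. This stands in part. A reader might infer that the follow-up data can get no valid comparison, or that any later test would be ad hoc. The document does not support that, because the type of test is fixed in advance. What is missing is the statement that it will be applied at those visits, and with what standing, when the section specific to these outcomes names V10 only.

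A second reply is that the phrase about changes before treatment is a wording slip. That is very probably right. A reader might infer from the literal wording that the ANOVA has no time points to work on and cannot be run. That argument attacks the slip rather than the plan. It also overlooks that 3.8.2 lists both a screening and a baseline ROM, although Table 1 shows only one ROM before treatment. The sentence speaks of differences in changes, so a group comparison may have been intended; if so, it is not stated.

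A third reply is that visit-level models for secondary outcomes in a condensed article about a small trial, called a pilot in its introduction, belong in the analysis plan. Silence would indeed be no finding. Here, though, the article itself fixes V10 and the within-group wording, and these do not fit its own endpoint definitions. An analysis plan that follows 3.9.3.2 inherits the gap; one that departs from it conflicts with the published text.

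**Conclusion.** The point holds in a limited form. No outcome-specific between-group contrast is assigned to any of the 9 secondary follow-up points or to K-WOMAC at FU2. The one longitudinal method is described as within a group, so as written it cannot show whether an acupuncture effect persists. This rests on the wording of 3.8.1, 3.8.2, 3.9.1, 3.9.3.1 and 3.9.3.2, and on no assumed effect size. It holds whether or not the ANOVA phrase is a slip.

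It does not mean that follow-up comparisons are impossible or would be invalid, and it says nothing against the V10 primary analysis. No figure for lost power is offered, because the document gives no effect size or between-visit correlation for these outcomes. The correction should be made, but it concerns supportive results rather than the trial's main conclusion.

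**What to change.** Replace the last sentence of 3.9.3.2 with a longitudinal model, for example a mixed model for repeated measures. It should contain group, visit, group-by-visit and the screening value of the outcome. Fit it to each outcome's visits after the start of treatment as scheduled in Table 1, and report the between-group difference with its 95% confidence interval at each:

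- K-WOMAC: V10, FU2
- NRS: V6, V10, FU1, FU2, FU3
- ROM: V6, V10, FU2, FU3
- physical tests: V10, FU3

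State four things alongside it, so that no comparison has two rules:

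1. The test in 3.9.3.1 remains the primary V10 analysis of K-WOMAC.
2. For secondary outcomes, the model's V10 contrast replaces the Student's *t* test.
3. Visits after V10 are supportive.
4. The model uses observed data. For these outcomes, last observation carried forward (3.9.1) serves only as a sensitivity analysis.

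The cost is protocol or analysis-plan wording and slightly more analysis work. No new data or participants are needed, and the primary comparison stays as it is.

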##### Safety variables

3.9.3.3

The number of adverse reactions (vital signs, abnormal values in a physical test, acute reactions observed after vaccination, and local or systemic reactions) will be determined for each group, and their incidence and 95% confidence intervals will be presented. The chi-square test will be used for intergroup comparisons of adverse reactions.

Continuous data such as blood or blood chemistry test parameters, physical test parameters, and vital signs will be presented for each group and assessed using descriptive statistics. A paired *t* test will be used for comparisons before and after the treatment, and Student's *t* test will be used for intergroup comparisons. The frequency and percentage will be presented for categorical data such as urine test results, and McNemar's test will be used to determine normal and abnormal conditions for each visit.

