## Introduction

1

Total knee replacement (TKR) is a surgical procedure that is being increasingly performed due to population aging and increased life expectancy in South Korea. The number of TKR procedures increased by over 135%, from 45,879 in 2015 to 62,344 in 2019. The medical cost of public health insurance associated with TKRs totaled 37,077,059,000 won (∼32,638,256 US dollars) in 2015 and increased to 55,499,427,000 won (∼48,850,829 US dollars) in 2019.^[1]^ The age distribution of patients undergoing TKR shows that 36.2% of the patients were aged 60 to 69 years, 48.6% were aged 70 to 79 years, and 8.7% were aged ≥80 years,^[2]^ indicating that TKR is primarily performed on elderly patients. A large number of patients undergo TKR due to degenerative knee arthritis. Consistent with the high incidence of TKR in South Korea, the number of patients seeking acupuncture for pain management and enhancement for rehabilitative therapy effects and bodily function not only before but also after TKR has also been increasing.

In the western-medicine-based clinical settings in South Korea, acupuncture treatment after TKR is considered unsafe regardless of the acupuncture points in use because of the risk of infection and reoperation, and the practice is often rejected or prohibited. Furthermore, according to a recent systematic review, including acupuncture in a rehabilitation program is beneficial as an adjunct to opioids for pain management across several types of postsurgical conditions.^[3]^ However, the results of studies investigating the effect of acupuncture after TKR are not in concordance.^[4–7]^ Moreover, no previous study has examined the efficacy, safety, and cost-effectiveness of post-TKR acupuncture rather than focusing solely on its efficacy.

Therefore, it is worth assessing the effectiveness, safety, and cost-effectiveness of acupuncture as an adjunctive therapy in patients following TKR in a pilot study.

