### Sample size calculation

3.3

In this clinical trial, changes in the K-WOMAC will be analyzed and assessed to examine the effect of acupuncture on pain and functional improvements in patients who underwent TKR.

Due to the lack of information about domestic clinical trials to examine the K-WOMAC as a primary outcome for assessing the effect of acupuncture on the knee joint, we referred to a study in which aromatherapy massage was performed on patients with knee arthritis (married women).^[8]^

The changes in the K-WOMAC after 2 weeks of aromatherapy massage or regular massage in the experimental and control groups were −6.10 ± 4.05 and 0.24 ± 4.16, respectively. The difference in the K-WOMAC between the groups was 6.34. In this study, the difference in the K-WOMAC between the experimental and control groups is assumed to be 3.60. We referred to previous studies for standard deviations. The level of statistical significance is set at 0.05 (α, two-tailed), and power (1−β) is set at 80%.

The minimum sample size needed to test the statistical significance was calculated using ‘G∗Power 3.1.9.2’ and was found to be 22 participants per group. Considering a 10% dropout rate, 25 participants per group or a total of 50 participants will be recruited.

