#### Safety and adverse events monitoring

3.8.3

The safety assessment includes

1.adverse reactions,2.vital signs, and3.clinical laboratory testing.

The subinvestigator will record the details of any adverse reactions and the use of concomitant medications during the clinical trial in the case report form. In case of an adverse reaction, the symptoms and signs of the adverse reaction, duration (start date/end date), severity, result, significance, causal relationship to the drug under clinical investigation, and measures taken for its alleviation will be recorded. The names, dosages, duration of administration, reason for administration, etc, of the concomitant medications will be recorded in detail.

Clinical laboratory tests will be performed at screening, V5, V9, FU2, and FU3. Since this study will evaluate the safety of the usual care and acupuncture combination, it differs from clinical studies that evaluate the safety and pharmacokinetic properties of drugs. Therefore, this study conducts clinical laboratory tests for the following items for the purpose of the standard safety lab test:

1.hematology: hemoglobin, hematocrit, red blood cell count, white blood cell count, and differential count, platelet count;2.serum chemistry: glucose fasting, aspartate aminotransferase (AST), alanine aminotransferase (ALT), blood urea nitrogen (BUN), electrolytes (sodium, potassium, and chloride), serum creatinine (SCr), erythrocyte sedimentation rate (ESR), C-reactive protein (CRP); and3.coagulation: D-dimer, fibrin degradation products (FDP);4.γ-glutamyl transpeptidase (γ-GTP), alkaline phosphatase, creatinine phosphokinase (CPK), uric acid, total bilirubin, total protein, albumin, osteocalcin, carboxy-terminal collagen crosslinks (CTX), urine analysis: pH, protein (albumin), glucose, leukocyte esterase, and blood were performed only at screening.

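### The planned comparison of mean CRP, ESR and white cell count between arms says almost nothing about infection in one to three of 25 patients; by-arm counts and a patient listing would show them

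*Protocol article*

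**What the plan says.** The Introduction gives the reason why acupuncture is often refused after this operation by Korean hospitals that practise western medicine: "acupuncture treatment after TKR is considered unsafe regardless of the acupuncture points in use because of the risk of infection and reoperation". Safety is part of the hypothesis in section 2.

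Section 3.8.3 puts white cell count and differential under hematology and "erythrocyte sedimentation rate (ESR), C-reactive protein (CRP") under serum chemistry. On timing it says: "Clinical laboratory tests will be performed at screening, V5, V9, FU2, and FU3".

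Section 3.9.3.3 sets the analysis. Continuous blood results are summarised descriptively for each group, and then: "A paired *t* test will be used for comparisons before and after the treatment, and Student's *t* test will be used for intergroup comparisons". Categorical results, with urine tests as the example, get frequencies, percentages and McNemar's test of normal against abnormal. The same section also counts adverse reactions by group, local and systemic reactions included, with 95% confidence intervals and a chi-square test.

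Two other sections bear on this. Section 3.9.1 prescribes the Wilcoxon rank-sum test for continuous variables that are not normal. Section 3.8.4 does not class as adverse reactions those symptoms that the principal investigator considers unrelated to the intervention, and it allows reactions to be put down to the knee replacement itself.

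**The concern.** Infection happens to individual patients; it does not shift a whole arm. A few very high values raise the arm's standard deviation along with its mean, so the t statistic levels off instead of growing. The comparison fixed in section 3.9.3.3 can therefore come out non-significant although several patients in one arm have grossly raised inflammatory markers.

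At stake is what the trial can say about the harm that its own Introduction names. The adverse-reaction count is the other place where an infection would appear. Under section 3.8.4, however, an infection attributed to the operation and not to acupuncture may be left out of that count. The laboratory values do not pass through that judgement, so how they are summarised by arm matters more than it otherwise would.

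**Working it through.** **Inputs from the protocol article.** Section 3.3: "Considering a 10% dropout rate, 25 participants per group or a total of 50 participants will be recruited"; the number before dropout "was found to be 22 participants per group". Sections 3.3 and 3.9.1: two-sided 5% level. The article gives no infection rate, so k = 1, 2 or 3 affected patients in one arm and none in the other is an assumed scenario.

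**The plan's own figure.** Section 3.3 says that "the difference in the K-WOMAC between the experimental and control groups is assumed to be 3.60", and the changes in the source study "were −6.10 ± 4.05 and 0.24 ± 4.16, respectively". The pooled SD is √((4.05² + 4.16²)/2) = 4.105. A two-sample t test at 80% power needs 21.4 per arm, so 22 (power 81.1%). Allowing for 10% dropout, 22/0.9 = 24.4, so 25. The stated size is reproduced; it was set for K-WOMAC, not for safety.

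**Ceiling on t.** Let k of n patients in one arm have the same value M, so large that all other variation is negligible.
- Mean difference: kM/n.
- Variance in that arm: M²·k(n−k)/[n(n−1)]; in the other arm, about 0.
- Standard error: (M/n)·√[k(n−k)/(n−1)].
- M cancels in the ratio, leaving t = √[k(n−1)/(n−k)].

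| k | t, n = 25 | p (48 df) | t, n = 22 |
|---|---|---|---|
| 1 | √(24/24) = 1.00 | 0.32 | 1.00 |
| 2 | √(48/23) = 1.45 | 0.16 | 1.45 |
| 3 | √(72/22) = 1.81 | 0.077 | 1.82 |
| 4 | √(96/21) = 2.14 | 0.038 | 2.16 |

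The critical value is 2.011 at n = 25 and 2.018 at n = 22. In the limit, four patients are needed at either size.

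**Finite values.** Simulation with a normal background, n = 25 and 40,000 runs per cell; rejection rate of the t test when k values are shifted by the stated number of SDs:

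| k | 5 SD | 10 SD | 20 SD | 100 SD |
|---|---|---|---|---|
| 1 | 4.5% | 2.3% | 0.1% | 0% |
| 2 | 8.9% | 6.4% | 0.9% | 0% |
| 3 | 17.3% | 19.8% | 13.2% | 0% |

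**Wilcoxon instead.** With shifts large enough that the affected patients always rank highest (8,000 runs), rejection is 4.8%, 6.3% and 8.4% for k = 1, 2 and 3. With no affected patient it is 4.7%. The Shapiro-Wilk test rejected normality in every simulated arm with one to three values shifted by 10 SD, so the rule in section 3.9.1 would be triggered if it covers safety data.

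**Counts instead.** Fisher's exact p for 1, 2 and 3 of 25 against 0 of 25 is 1.00, 0.49 and 0.23. It first falls below 0.05 at 6 v 0 (5 v 0 gives 0.0502).

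**What a count would report.** For 3/25 the estimate is 12%, with an exact (Clopper-Pearson) 95% interval of 2.5% to 31.2%. For 0/25 the upper limit is 1 − 0.025^(1/25) = 13.7%. These figures show both the affected patients and how little 25 patients can exclude.

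**The case against.** The strongest objection is that the test is not the cause. With 25 per arm nothing detects 3 v 0, and the count test is no more sensitive. That stands. A reader might infer that Student's t test should give way to a better test; the figures do not support this.

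Second, out-of-range tables and listings are commonly left to a full protocol or analysis plan, which is not shown. Their absence from the article is therefore no finding, and the descriptive statistics in section 3.9.3.3 do not exclude them. This also stands. The point rests on the comparison that is stated, which suits rare individual events badly.

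Third, the article has other routes to an infection. Section 3.9.3.3 counts local and systemic reactions with confidence intervals. Section 3.9.3.4.4 names surgical site infection as a dropout case that stays in the ITT analysis. Section 3.8.4 lists infection diagnosed in the recovery room as a dropout criterion. The normal/abnormal frequencies might also extend to blood tests, because urine analysis is done only at screening and cannot supply a result for each visit. These routes weaken the concern without removing it: the reaction count is subject to the attribution rule, and McNemar's test compares visits within patients, not arms.

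Three further readings are tempting and go too far.
- *These markers are the only infection measures free of attribution.* Vital signs are also collected without it.
- *The t test can never flag such patients, however extreme.* That is exact only in the limit; the simulation gives up to about 20% rejection for three patients.
- *The investigators will present a non-significant result as proof of safety.* The article does not say so.

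**Conclusion.** The concern holds in a limited form. The between-arm comparison of CRP, ESR and white cell count in section 3.9.3.3 is uninformative about infection in one to three of 25 patients, whether done by t test or by Wilcoxon. The sections that name those two tests do not agree and should be reconciled. The cause is the arm size together with a summary by means, so no change of test cures it. What can be improved is what is displayed and how a non-significant result is read.

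The conclusion assumes affected patients in one arm only and, for the simulated rates, a normal background. The limiting t values do not depend on the background. Severity is minor: the data are already scheduled, the adverse-reaction analysis covers part of the ground, and an analysis plan may already contain the listings.

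**What to change.** In section 3.9.3.3, for CRP, ESR and white cell count:

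- Report by arm the number and percentage of patients above the laboratory's own upper limit, chiefly at FU2 and FU3, with exact 95% confidence intervals for each arm and for the difference.
- List those patients individually, whatever the causality rating.
- Treat V5 and V9 as descriptive, because raised values are to be expected in both arms soon after surgery and a count there would not single out infection.
- State that a non-significant comparison of means is not evidence that infection is absent.
- Say whether the Wilcoxon rule in section 3.9.1 applies to safety data, so that the two sections name the same test.

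The cost is a few extra safety tables and one listing, from samples already scheduled. No visit, assay or sample size changes, and nothing in patient care is affected.
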